### Patient recruitment

2.2

A total of 200 Chinese women who received primary therapy for breast cancer and commence tamoxifen within the past month will be recruited for this study. The inclusion criteria for the patients are: Chinese women with histologically confirmed estrogen receptor-positive, stage I–III, primary invasive breast cancer treated with definitive surgery and/or chemotherapy and started on tamoxifen (20 mg daily) within the past month. We will exclude patients with other cancers within the last 5 years. In addition, patients who are pregnant or are planning to become pregnant, lactating, treated with investigational drugs within the 4 weeks before enrolment, as well as those who are not able to provide written informed consent will be excluded. The participating hospitals have 600 new cases of breast cancer per year and half of these patients will be prescribed tamoxifen. It is anticipated that 100 to 150 patients will be recruited per year based on our experience with the pilot study.

### Ethical considerations

2.3

This study was registered on the ISRCTN Registry with reference number ISRCTN10773849. The study protocol was approved by the Joint Chinese University of Hong Kong—New Territories East Cluster Clinical Research Ethics Committee with reference number 2016.554. Any modifications to the protocol that may have an impact on the conduct of the study will be reported to the committee. Potential patients will be given detailed information about the study and their rights to participate (Supplemental Digital Content (Appendix 1)). Written informed consent will be obtained before data collection (Supplemental Digital Content (Appendix 2)).

### Sample size estimation

2.4

The sample size was calculated to provide adequate power to examine associations between genetic polymorphisms and severity of endocrine symptoms associated with tamoxifen treatment, as well as adherence with tamoxifen treatment. In general, a larger sample size for an association analysis allows for the detection of a smaller effect size at a specific statistical power and level of significance. However, a small effect size may not be of clinical importance. In consideration of both clinical relevance and statistical power, we aim to detect a reasonable effect size of *R*^2^ = 0.05 for a genetic predictor of severity of endocrine symptoms of tamoxifen treatment as well as for an association between the severity of endocrine symptoms and level of adherence with tamoxifen treatment.

Using PASS 13 (NCSS, Kaysville, UT), it is estimated that a sample size of 152 patients would give our study 80% power at a 5% level of significance to detect an effect size of *R*^2^ = 0.05 (ie, if a specific polymorphism explains at least 5% of the variance in the severity of symptoms of tamoxifen treatment or if the severity of symptoms explains 5% of variance in adherence to the treatment, they will be detectable with 80% power at 5% significance level).

Since our follow-up measurements are based on brief telephone interviews, we anticipate that the nonresponse rate will be relatively low. In fact, all of the patients completed the 3-month follow-up in our ongoing pilot study. Furthermore, on the basis of a 1-year crude death rate of breast cancer patients in Hong Kong (4.4%) (WHO, http://survcan.iarc.fr/index.php) and assuming an average non-response rate for our follow-up questionnaires of <3% for every 3 months, we anticipate that the overall attrition rate in our 18-month prospective cohort study will be 24%. Therefore, we will recruit 200 eligible patients into the study.

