### Genomic assessment

2.6

At enrolment, saliva samples will be collected from patients and stored in a −80°C freezer. Total genomic DNA will be extracted from the saliva using QIAamp DNA Mini Kit (Qiagen, USA) as per supplier's instructions. Genotype analyses will be carried out with ready-to-order TaqMan assays from Thermo Fisher. All patients will be tested for allelic variations in 2 cytochrome P450 enzyme genes (ie, UDP glucuronosyl transferase and sulfotransferase) and 14 drug transporter genes (ie, CYP3A4, CYP3A5, CYP2C9, CYP2C19, CYP2D6, CYP1A2, CYP2B6, UGT1A4, UGT2B7, UGT1A8, UGT2B15, ABCC1, ABCB1, ABCC2). These SNPs were selected because they were reported to be involved in tamoxifen metabolism, which may affect the occurrence and severity of endocrine symptoms.^[20,22]^

Based on the available genotype data, CYP2D6 alleles (as an example) will be assigned a value that reflects the expected activity of the CYP2D6 enzyme for which they code. For example, fully functional CYP2D6 alleles (eg, ∗1, ∗2, ∗33, ∗35) will be assigned a score of 1. CYP2D6 alleles associated with reduced enzyme activity (eg, ∗9,∗10, ∗17, ∗29, ∗37, ∗41, ∗45, ∗46) will be scored as 0.5. The null CYP2D6 alleles (eg, ∗3-∗8, ∗11-∗16, ∗18-∗20, ∗38, ∗40, ∗42, ∗44, ∗56) and their duplications will receive a value of 0. Duplications of fully active alleles (eg, ∗1×N, ∗2 × N, ∗35 × N) will be assigned a value +1, rendering a score of 2 for each of these duplicated variants. Duplicated reduced activity alleles (eg, ∗41 × N and ∗45 × N) will be assigned a value of +0.5, yielding a score of 1.^[35]^

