The genetic factors will be examined as individual SNPs and haplotypes of SNPs from different candidate loci, as appropriate. The distribution of genotypes in candidate SNPs will be tested for Hardy–Weinberg equilibrium (HWE) using Fisher exact test. SNPs in conformation with HWE will be used in regressions analyses to determine their relative contribution to the overall severity of the symptoms associated with tamoxifen treatment with adjustment for potential confounders, including age, menopausal status, stage of cancer at diagnosis, and treatment received. The linkage disequilibrium between SNPs in candidate loci will be analyzed using Haploview (Daly Lab, Cambridge, MA) and haplotypes will be created. The relationships between these haplotypes and overall severity of the symptoms of tamoxifen will be analyzed by the regression-based approach of Zaykin et al^[36]^ after adjusting for potential confounders with the use of a permutation test. Statistical significance will be evaluated using permutations with 10,000 replications. Inflated overall type I error rate will be controlled using the approach of Benjamini and Hochberg.^[37]^ Furthermore, multivariable regression analysis will examine the associations between overall adherence with tamoxifen treatment and overall severity of the symptoms of tamoxifen treatment with adjustment for the above potential confounders. All statistical analyses unless otherwise specified will be performed using SAS release 9.4 (SAS Institute, Cary, NC). All statistical tests will be 2-sided and a *P* value <.05 will be considered statistically significant.

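### The 80% power holds for a single test at an unadjusted 5%, so it covers the symptom-adherence association but not the multiplicity-corrected SNP and haplotype tests

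*Protocol article*

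**What the plan says.** Section 2.4 (Sample size estimation) states that "it is estimated that a sample size of 152 patients would give our study 80% power" at the 5% level for R² = 0.05. It applies this to two associations. One is genetic, "if a specific polymorphism explains at least 5% of the variance in the severity of symptoms of tamoxifen treatment"; the other is symptom severity explaining 5% of the variance in adherence. For both it concludes that "they will be detectable with 80% power at 5% significance level". With 24% attrition, 152 becomes 200 recruited. The section does not mention multiple testing.

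Section 2.6 (Genomic assessment) describes a panel of 2 genes plus "14 drug transporter genes", and the list for the second group names 14. It gives no SNP count and names no primary polymorphism.

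Section 2.7 (Data analysis) examines individual SNPs and haplotypes against overall symptom severity, after removing SNPs that fail Hardy-Weinberg equilibrium. It then says: "Inflated overall type I error rate will be controlled using the approach of Benjamini and Hochberg". It closes with "All statistical tests will be 2-sided" and the rule that a P "value <.05 will be considered statistically significant".

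**The concern.** The sample size section assumes one test at 5%, while the analysis section plans many genetic tests with a correction. A SNP that explains 5% of symptom variance must therefore pass a stricter threshold than the one used to compute 80%. Both statements are printed in the article, so this is a mismatch between two sections and not a detail left to a fuller document.

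The genetic association is one of the study's two hypotheses. A reader who accepts 80% power would take a null SNP result as fair evidence against an effect of R² = 0.05, when the planned analysis may miss such an effect about half the time.

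Two wording problems sit beside this. Benjamini-Hochberg controls the false discovery rate, but the text says it controls the overall type I error rate. The closing .05 rule does not say whether it applies to raw or adjusted P values.

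**Working it through.** **Inputs from the article.** Two-sided α = 0.05, R² = 0.05, 152 analysable patients and 24% attrition (sections 2.4 and 2.7); Benjamini-Hochberg correction (section 2.7).

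**Assumption.** The number of tests m is not given. I take m = 14 (one SNP per listed gene) or m = 16 (2 + 14 genes), with independent tests, and show larger values.

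**Step 1: reproduce the stated figure.** For one predictor in a linear regression, f² = R²/(1 − R²) = 0.05/0.95 = 0.0526. The noncentrality is λ = n·f² = 152 × 0.0526 = 8.0. Power is the probability that a noncentral F(1, n − 2; λ) exceeds the central critical value at α.

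- n = 151: power 0.7998.
- n = 152: power 0.8024.

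So 152 is the smallest n that reaches 80%, and 152/0.76 = 200. Both figures reproduce, but only for a single one-degree-of-freedom test at an unadjusted 5%.

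**Step 2: apply the strictest Benjamini-Hochberg step.** If only one SNP is truly associated, its P value must usually fall below about 0.05/m. The same formula with α = 0.05/m gives:

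| m | 0.05/m | Power at n = 152, R² = 0.05 |
|---|---|---|
| 1 | 0.0500 | 80.2% |
| 14 | 0.0036 | 45.0% |
| 16 | 0.0031 | 43.3% |
| 20 | 0.0025 | 40.6% |
| 30 | 0.0017 | 35.9% |
| 40 | 0.0013 | 32.7% |

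**Step 3: simulate the actual step-up procedure.** Benjamini-Hochberg at 0.05, independent tests, n = 152, 100,000 replicates, each true SNP with R² = 0.05. Power per true SNP:

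| Truly associated SNPs | m = 14 | m = 16 |
|---|---|---|
| 1 | 46% | 44% |
| 2 | 51% | 49% |
| 3 | 55% | 53% |
| 5 | 62% | 60% |
| 7 | 67% | 65% |

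Even if all 14 or all 16 SNPs had R² = 0.05, per-SNP power would be 77%.

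**Step 4: allow for covariates.** If the adjustment variables explain a share c of outcome variance and the SNP explains 5% of the total, f² = 0.05/(1 − c − 0.05). The values of c are my assumption.

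- c = 10%: f² = 0.05/0.85 = 0.0588, λ = 8.9. Power at 0.05/m is 51% (m = 14) or 50% (m = 16).
- c = 30%: f² = 0.05/0.65 = 0.0769, λ = 11.7. Power is 68% or 66%.

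**Step 5: what the sample can detect.** For a lone SNP at 0.05/m and n = 152, the R² detectable with 80% power is 0.087 (m = 14) or 0.089 (m = 16). Keeping R² = 0.05 would need 273 analysable patients (273/0.76, so 360 recruited) or 279 (279/0.76, so 368 recruited).

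**Step 6: what Benjamini-Hochberg controls.** In the same simulation, the chance of at least one false positive is about 5% when no SNP is associated. With three true SNPs it is about 10.5% (m = 14: 10.5%; m = 16: 10.7%). The overall type I error rate is therefore not held at 5% once true effects exist.

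**The case against.** Several objections carry weight.

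- **The arithmetic is not wrong.** Section 2.4 states its condition openly, a specific polymorphism at the 5% level, and as a per-comparison statement it is true. This stands. The fault is the mismatch with section 2.7.
- **Half of the sentence is unaffected.** The symptom-adherence association is one test, so its 80% holds. This stands.
- **A reader might infer that power is 45% at most.** The documents do not support that ceiling. It describes a lone true SNP among 14 or more tests, with covariates explaining nothing. The loci were chosen because they were reported to be involved in tamoxifen metabolism, so several true associations are possible, and then per-SNP power is higher. The chance of finding at least one of three true SNPs is about 84-85%. Taken one at a time, the scenarios above all stay below 80% per SNP. Combining favourable ones can pass it: seven true SNPs, 14 tests and covariates explaining 20% give about 80%, and 30% gives about 86%. Section 2.4 claims nothing of that kind.
- **A reader might infer that the two sentences in section 2.7 contradict each other.** They need not. A Benjamini-Hochberg adjusted P value compared with .05 satisfies both. The text is ambiguous and should say so.
- **The number and dependence of the tests are unknown.** Dropped SNPs would reduce m, while extra SNPs per gene and haplotypes would raise it. Linkage disequilibrium makes independent-test results approximate. This is why a range is needed.
- **The correction sentence follows the haplotype text.** Applying it to single SNPs is the natural reading but is not spelled out. If it did not apply, the single-SNP tests would have no correction at all.
- **The study describes its output as preliminary evidence.** That softens the consequence but does not make the stated power right for the genetic aim.

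**Conclusion.** The concern holds in a limited form. The figures 152 and 200 are correct, and 80% stands for the symptom-adherence association. It does not describe the planned genetic analysis. Assuming 14 to 16 independent tests, power for R² = 0.05 is about 44-46% for a lone true SNP and about 49-67% per SNP with two to seven true SNPs. It falls to about 33% for a lone SNP with 40 tests, and reaches about 50-68% for a lone SNP if covariates explain 10-30% of the variance. The R² detectable with 80% power for a lone SNP is about 0.09, not 0.05.

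These figures depend on the assumed number of tests, their independence, and a one-degree-of-freedom test per SNP. The direction does not: any correction for several tests puts a lone SNP below its uncorrected power. The description of Benjamini-Hochberg as controlling the overall type I error rate is inaccurate, and the .05 rule is ambiguous but not contradictory.

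**What to change.** In section 2.4, keep 152 and 200. State the number of SNP and haplotype tests planned. Limit the 80% claim to the symptom-adherence association, and to a single polymorphism only before correction. Add a corrected statement for the genetic aim as a range with its assumptions, for example: with 14 to 16 independent tests, about 44-46% power for R² = 0.05 if one SNP is associated and about 49-67% per SNP if two to seven are; detectable R² for a lone SNP about 0.09. Update the range once the SNP count is fixed.

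In section 2.7, replace the reference to the overall type I error rate with the false discovery rate. Say that the correction covers both SNP and haplotype tests. Say that the .05 cut-off applies to Benjamini-Hochberg adjusted P values for the genetic tests and to the unadjusted P value for the adherence model.

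Naming one primary polymorphism is not required. The study began in November 2016, so it would be a late choice. The cost is wording and a less favourable stated power for the genetic aim, with no extra patients and no change to data collection.

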### Clinical assessments

2.5

Three kinds of clinical data will be collected from the patients.

#### Symptoms

2.5.1

Endocrine symptoms will be assessed using the Greene Climacteric Scale (GCS) and the Functional Assessment of Cancer Therapy-Endocrine subscale (FACT–ES) questionnaire (version 4) from the FACIT system. The GCS is a 21-item self-administered instrument that contains 4 domains (ie, psychological, somatic, vasomotor, sexual). Each item is rated on a 3-point scale (1 = a little to 3 = extremely), indicating the severity of the symptoms experienced. The mean score for each domain will be calculated. The GCS has good internal consistency and test–retest reliability.^[27]^ Psychometric properties of the Chinese version were reported previously.^[28]^

The FACT-ES is a 19-item questionnaire that measures menstrual symptoms, such as vaginal dryness and spotting. These menstrual symptoms are not included in the GCS. The internal consistency and test–retest reliability of the Chinese version of the FACT-ES is published.^[29]^ Patients will be interviewed using the GCS and FACT-ES at enrolment and again at 3, 6, 9, 12, 15, and 18 months.

#### Drug adherence

2.5.2

The Modified Medication Adherence Report Scale (MMARS) will assess the patients’ level of adherence with tamoxifen. The Medication Possession Ratio (MRP) will be used to cross-validate this self-report measure. MARS assesses patients’ attitudes toward medication, perceived benefits from medications, and insights into their illness. The modified MARS (MMARS) contains 6 items selected from the 22-item MARS that pertains to patients’ level of adherence with medication behaviors and attitudes. The Cantonese version of this scale will be used in this study.^[30]^

The MPR^[31]^ is calculated as the sum of the day's supply of all relevant medications during a defined period of time divided by the number of days elapsed during that period of time. This ratio is used frequently to evaluate drug adherence. Given the variability in the severity of tamoxifen-related endocrine symptoms and the need to take the drug daily for a long period of time, MPR rates will be defined as good if >72% of the tamoxifen is taken, normal if 41% to 72% is taken, and poor if <41% is taken.^[14,32–34]^ Patients will be asked to complete a medication diary on a daily basis to record the intake of tamoxifen, supplements, Chinese herbal medicines, and other medications, and to complete the drug refill form. This information will be collected every 3 months by a research assistant.

#### Demographic and clinical characteristics

2.5.3

Demographic and clinical characteristics will be collected at enrolment by self-report. This information includes: education and socioeconomic status, height and weight, menopausal status, smoking, alcohol use, parity, level of physical activity, medications, comorbidities, self-medications (eg, home remedies, over the counter remedies, dietary supplements, Chinese medicine), stage of breast cancer, tested for BRCA1/2, family history of breast cancer, and history of oophorectomy. At 12 and 18 months, information on breast cancer recurrence will be collected during the phone interview.

### Genomic assessment

2.6

At enrolment, saliva samples will be collected from patients and stored in a −80°C freezer. Total genomic DNA will be extracted from the saliva using QIAamp DNA Mini Kit (Qiagen, USA) as per supplier's instructions. Genotype analyses will be carried out with ready-to-order TaqMan assays from Thermo Fisher. All patients will be tested for allelic variations in 2 cytochrome P450 enzyme genes (ie, UDP glucuronosyl transferase and sulfotransferase) and 14 drug transporter genes (ie, CYP3A4, CYP3A5, CYP2C9, CYP2C19, CYP2D6, CYP1A2, CYP2B6, UGT1A4, UGT2B7, UGT1A8, UGT2B15, ABCC1, ABCB1, ABCC2). These SNPs were selected because they were reported to be involved in tamoxifen metabolism, which may affect the occurrence and severity of endocrine symptoms.^[20,22]^

Based on the available genotype data, CYP2D6 alleles (as an example) will be assigned a value that reflects the expected activity of the CYP2D6 enzyme for which they code. For example, fully functional CYP2D6 alleles (eg, ∗1, ∗2, ∗33, ∗35) will be assigned a score of 1. CYP2D6 alleles associated with reduced enzyme activity (eg, ∗9,∗10, ∗17, ∗29, ∗37, ∗41, ∗45, ∗46) will be scored as 0.5. The null CYP2D6 alleles (eg, ∗3-∗8, ∗11-∗16, ∗18-∗20, ∗38, ∗40, ∗42, ∗44, ∗56) and their duplications will receive a value of 0. Duplications of fully active alleles (eg, ∗1×N, ∗2 × N, ∗35 × N) will be assigned a value +1, rendering a score of 2 for each of these duplicated variants. Duplicated reduced activity alleles (eg, ∗41 × N and ∗45 × N) will be assigned a value of +0.5, yielding a score of 1.^[35]^

### Data analysis

2.7

Data will be summarized using appropriate descriptive statistics. Continuous data will be assessed for skewness and kurtosis and normal probability. Appropriate transformations will be made for skewed variables before entering them into the statistical analysis.

Since an episode of drug adherence might not reflect an overall adherence rate of a medication for an extended duration, a summary measure based on the area under the curve (AUC) of repeated measures of tamoxifen treatment adherence assessed using MMARS over 18 months (ie, specifically at months 3, 6, 9, 12, 15, 18) will be used to quantify overall adherence with tamoxifen treatment. Likewise, the AUC for each of the items on the GCS and the FACT-ES that are measured at enrolment, 3, 6, 9, 12, 15, 18 months will be computed first to obtain an overall measure of the severity of each symptom.

Since some highly correlated items may exist in the GCS and FACT-ES, a principal component factor analysis will be conducted on the AUCs of the GCS and FACT-ES items to identify uncorrelated principal components. These principal components can be regarded as the latent factors that give rise to the reported symptoms. Since no previous evidence exists regarding which symptom has a larger effect on adherence with tamoxifen, equal weighting will be given to each principal component. Then, the standardized factor scores computed using the Anderson-Rubin method of the principal components identified will be summed to quantify the overall severity of the symptoms associated with tamoxifen treatment.

The genetic factors will be examined as individual SNPs and haplotypes of SNPs from different candidate loci, as appropriate. The distribution of genotypes in candidate SNPs will be tested for Hardy–Weinberg equilibrium (HWE) using Fisher exact test. SNPs in conformation with HWE will be used in regressions analyses to determine their relative contribution to the overall severity of the symptoms associated with tamoxifen treatment with adjustment for potential confounders, including age, menopausal status, stage of cancer at diagnosis, and treatment received. The linkage disequilibrium between SNPs in candidate loci will be analyzed using Haploview (Daly Lab, Cambridge, MA) and haplotypes will be created. The relationships between these haplotypes and overall severity of the symptoms of tamoxifen will be analyzed by the regression-based approach of Zaykin et al^[36]^ after adjusting for potential confounders with the use of a permutation test. Statistical significance will be evaluated using permutations with 10,000 replications. Inflated overall type I error rate will be controlled using the approach of Benjamini and Hochberg.^[37]^ Furthermore, multivariable regression analysis will examine the associations between overall adherence with tamoxifen treatment and overall severity of the symptoms of tamoxifen treatment with adjustment for the above potential confounders. All statistical analyses unless otherwise specified will be performed using SAS release 9.4 (SAS Institute, Cary, NC). All statistical tests will be 2-sided and a *P* value <.05 will be considered statistically significant.

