The optimal management strategy for tamoxifen is one that considers the balance between the drug's potential benefits and adverse effects. The way that tamoxifen is metabolized and its potential toxicities are partially influenced by each patient's genetic makeup.^[43]^ The aim of this study is to determine whether, and how, symptoms of tamoxifen correlate with drug adherence and with polymorphisms in genes that regulate the metabolism of tamoxifen in Chinese breast cancer patients. We hypothesize that patients with more severe endocrine symptoms (ie, psychological, somatic, vasomotor, sexual) are less likely to adhere to tamoxifen treatment. In addition, we hypothesize that a relationship exists between the severity of tamoxifen-induced symptoms and allelic variations in tamoxifen metabolism-related genes. To date, studies have focused primarily on the associations between genetic polymorphisms and tamoxifen efficacy^[44,45]^ and not on the association between these factors and tamoxifen-induced symptoms and subsequent adherence. Adherence could be improved by understanding the factors that are associated with patients who are less likely to adhere and any modifiable factors (eg, barriers and facilitators) to their adherence.^[46]^ This increased understanding could contribute to the development of individualized symptom management interventions for patients who are prescribed tamoxifen, ultimately leading to greater adherence and reduced risks of breast cancer recurrence and death.

This study is significant in that it will provide preliminary evidence on the factors associated with tamoxifen adherence in Chinese breast cancer patients. The results of this study may lead to larger descriptive and interventional studies that will evaluate different approaches to increase tamoxifen adherence rates and its clinical efficacy.

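### Overall symptom severity is an equal-weight sum of uncorrelated component scores with no rotation or sign rule, so taken as written a higher score need not mean worse symptoms

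*Protocol article*

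**What the plan says.** Section 2.7 computes an AUC over follow-up for each GCS and FACT-ES item and extracts uncorrelated principal components from these AUCs. By section 2.5.1 there are 21 + 19 = 40 items. The severity measure is then defined as follows: "the standardized factor scores computed using the Anderson-Rubin method of the principal components identified will be summed to quantify the overall severity". On the weights, and on the grounds that nothing is known about which symptom affects adherence more, the section says that "equal weighting will be given to each principal component".

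The same section uses this sum as the outcome of the SNP and haplotype analyses and as the predictor in the adherence regression. It gives no rotation, sign orientation, retention rule or number of components.

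Section 2.5.1 says of the GCS that "The mean score for each domain will be calculated". The Discussion frames the adherence hypothesis around the same four domains: "patients with more severe endocrine symptoms (ie, psychological, somatic, vasomotor, sexual) are less likely to adhere". The inferential analyses described in 2.7 use only the overall sum.

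Section 2.4 bases the sample size on a "reasonable effect size of *R*^2^ = 0.05 for a genetic predictor of severity of endocrine symptoms", and states that "it is estimated that a sample size of 152 patients would give our study 80% power at a 5% level of significance".

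**The concern.** Anderson-Rubin scores are mutually uncorrelated and each has variance 1. Three things follow when they are simply added.

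- **Direction.** The sign of a principal component is mathematically arbitrary. In an unrotated solution for positively correlated symptoms, the first component is general severity. The later ones set some symptoms against others, so neither sign means worse, and adding them does not add severity.
- **Weight.** The first component may explain a large share of the item variance and the last one kept very little, but both enter with weight 1.
- **Rationale.** Not knowing which symptom matters more is a reason for equal weights on symptoms. It is not a reason for equal weights on components, which is a different weighting of the items.

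Both study hypotheses rest on this score. If it tracks severity poorly, a null genetic or adherence result could come from the way the score is built, and the direction of a positive result would be hard to interpret.

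**Working it through.** **1. The plan's own figure.** Inputs from 2.4 and 2.7: R² = 0.05, two-sided 5%, 80% power, 24% attrition. For one predictor in a linear regression, power comes from the noncentral F distribution with 1 and N − 2 degrees of freedom and noncentrality N·R²/(1 − R²). At N = 152 the noncentrality is 152 × 0.05/0.95 = 8.0 and power is 80.2%. Inflation gives 152/0.76 = 200. Both stated figures reproduce.

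**2. Algebra of the sum.** Let r_j be the correlation of a SNP with component j, s_j = ±1 the sign of that component, and k the number kept. The sum has variance k, so

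R²(sum) = (Σ s_j r_j)² / k.

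The result depends on the relative signs. Reversing all signs together changes no two-sided P value. As an illustration, spread a total R² of 0.05 equally over k = 4 components, with N = 152:

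| Components with flipped sign | R² of the sum | Power |
|---|---|---|
| 0 | 0.05 | 80% |
| 1 | 0.0125 | 28% |
| 2 | 0 | 5% |

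**3. A general-severity effect in the unrotated solution.** Here severity sits almost wholly on the first component. The sum's correlation with it is ±1/√k, which is 0.447 at k = 5.

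The article does not give the symptom structure, so one is assumed: 40 items in 5 domains of 8; each domain has 40% of its variance from a general severity factor; each item has 50% of its variance from its domain; the SNP explains 5% of the general factor; n = 152; 5 components kept.

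- Variance of the item mean: 0.5 × (0.4 + 0.6/5) + 0.5/40 = 0.2725.
- Part due to general severity: 0.5 × 0.4 = 0.20, a share of 0.734.
- R² of the SNP on the item mean: 0.734 × 0.05 = 0.0367, power 67%.
- R² on the unrotated sum: 0.0367/5 = 0.0073, power 18%.

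**4. Simulation of the same structure (1,000 data sets).**

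| Severity score | Mean correlation with item total | Power |
|---|---|---|
| Item total | 1.00 | 66% |
| First component, sign fixed | 0.999 | 67% |
| Unrotated sum, first component positive, other signs random | 0.45 | 19% |
| Unrotated sum, each component signed so its loadings sum to a positive value | 0.48 | 18% |
| Varimax sum, all signs aligned to severity | 0.999 | 66% |
| Varimax sum, random signs | −0.01 | 16% |

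In 78% of the 300 data sets examined for this, whether the SNP reached P < 0.05 depended on the signs given to components 2 to 5. Signing each unrotated component by its loadings does not help, because the later components are contrasts whichever way they point.

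Over the range of assumed structures tried, power was about 15-20% for the unrotated sum and about 49-74% for the item mean or first component.

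**5. An effect confined to one domain.** In a separate simulation (40 items, 5 domains of 8, loading 0.75, factor correlation 0.2 to 0.6, n = 152, SNP R² = 0.05 on one domain), power was 10-13% for the varimax sign-aligned sum, 11-14% for the item mean, 11-15% for the first component and 74-78% for that domain's own mean.

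**The case against.** The strongest reply is that section 2.7 does not say the components are unrotated. It treats them as latent factors behind the reported symptoms, which fits rotated, oriented factors, and an article commonly leaves rotation and retention to the analysis plan. With varimax and aligned signs, the sum matches the item total (66% power each). This stands as a limit on the finding: the loss is conditional on taking the text as written. It does not remove the point. The equal-weight sum itself is fixed in the article, it measures severity only if both steps are added, and its stated reason concerns symptoms.

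Two stronger readings are tempting.

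- A reader might infer that the sum always divides a real effect by k, and that the stated 80% power is therefore false. The documents do not support this. Section 2.4 speaks of the severity of symptoms, and the natural reading is 5% of the variance of the analysed score, for which 152 is right. An effect spread evenly over rotated, aligned components is not diluted.
- A reader might blame the Anderson-Rubin sum for low power against a single-cluster effect. Step 5 shows that any overall score has this weakness, including the item mean recommended here. It is the price of asking about overall severity.

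Nor can it be said that the GCS domain means go unused: section 2.7 plans descriptive summaries, where they may appear. What is visible is only that the described regressions do not use them.

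**Conclusion.** The concern holds in a conditional form. As written, with no rotation or sign rule, the composite is not a dependable measure of overall severity. A higher value need not mean worse symptoms, and significance can turn on arbitrary signs. Under the assumed structures, the sum correlates about 0.45 in absolute value with the item mean, and power for a general-severity SNP effect is about 15-20% instead of about 49-74%. These sizes rest on assumed loadings and on about 5 components being kept, neither of which is in the article. The dependence on relative signs is algebra and needs no such assumption. Rotation with signs aligned to severity removes the loss. The equal weighting of components is not supported by the reason given for it. The sample-size calculation stands if R² = 0.05 refers to the analysed score.

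**What to change.** Define overall severity as the mean of the standardized item AUCs, all coded so that higher is worse. The first unrotated component, oriented to positive loadings, is an acceptable alternative. Either one gives the symptoms a direct and interpretable weighting.

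If the summed scores are kept, specify the rotation and orient every component so that higher means worse before adding. State both rules before the genetic data are analysed.

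To address cluster-specific effects, which no overall score detects well, analyse the four GCS domain scores and the FACT-ES score as secondary outcomes within the Benjamini-Hochberg control already planned.

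The cost is analysis wording only, with no new data. The downside is a larger multiplicity family: five further outcomes add about five times as many SNP and haplotype tests as the overall score alone.
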